### Study design, setting, and registration

2.1

Our clinical study is designed as a single-centered observational descriptive feasibility trial focusing on the user experience, safety and the performance of the system. Our study will be conducted at the Reha Rheinfelden in compliance with the Declaration of Helsinki, the ISO14155 standard, the guidelines of the International Council for Harmonisation for good clinical practice as well as national legal and regulatory requirements.

The study received approval from the independent ethics committee of Northwestern and Central Switzerland (EKNZ, reference number: 2024-D0028, BASEC Project-ID 2024-D0028) and the competent authority Swissmedic (reference number: 10001354). The study is registered with the Swiss National Clinical Trial Portal (SNCTP000005943), EUDAMED (CIV-CH-24-05-046954), and clinicaltrials.gov (NCT06449612).

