### Patients and recruitment

2.2

Patients' eligibility criteria are listed in Table 1 below.

**Table 1 T1:** Patients' (primary end-users) inclusion and exclusion criteria.

Inclusion criteria	Exclusion criteria
• Age ≥18 years • Clinically confirmed stroke • Modified Rankin Scale score 1–5 • Able, to read and understand German • Owns a smartphone or a tablet operating on Android version 11/iOS version 14 or higher	• Severe aphasia • Clinically significant concomitant disease states: visual, neurological, cardiorespiratory, psychiatric, or orthopedic limitations that prevent a participant from following the investigator's instructions or limit performance in an exercise program • Recent events such as surgery or other surgical procedures, fractures, which limit the performance in an exercise program • Known or suspected non-compliance, drug or alcohol abuse • Participation in another investigation (with interventional therapy, investigational drug or another medical device) within the 30 days preceding and during the present investigation

For recruitment, we use pragmatic consecutive sampling. During the recruitment period, every inpatient after stroke, who fulfils our eligibility criteria, has the opportunity to participate in the study. Patients will be informed about the study in oral and written form. After a minimum of 24 h, patients will be asked to provide written informed consent for the enrollment in the study. Data collection will start, and three sessions will be scheduled over a period of two to three weeks during inpatient stay. The recruitment period will run from July 2024 to 31. March 2025. No compensation for study participation will be provided.

Study participation will be immediately terminated if one of the following events occurs:
•The patient withdraws written consent.•The patient decides to withdraw from the study.•The project team members may exclude a patient from the investigation if any physical or mental condition is present that prevents the patient from participating in the study.Withdrawal of full consent means that the patient does not wish or is unable to participate further in the feasibility study. Data collected up to withdrawal of consent will be used for analysis.

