#### START program during inpatient rehabilitation

2.3.1

Besides their multi-disciplinary therapy schedule, patients will receive two to three practice sessions with a therapist lasting 30 to 60 min during three to two weeks before discharge. The intended activities during the sessions are described in Table 2.

**Table 2 T2:** Overview on the practice sessions to get to know the blended clinic application.

Practice session 1	• Onboarding: Under supervision, patients download and set up the mobile application Blended Clinic with the START program on their own smartphone or tablet. They will receive a written short guide for the application including user-friendly explanations with large font size and pictures. • Under supervision, patients learn how to use the application: ○ open, close and navigate through the application menus, ○ read and enter messages for the communication with the personal coach, ○ perform the self-measurement of the blood pressure values and enter the data in the mobile application • Under supervision, patients perform one to eight exercises of their individualized exercise program that was selected by the therapist or coach based on the patient's goal. • Study personnel sets up the activity tracker.
Practice session 2	• Under supervision, patients practice to interact with and navigate through the application menus (open training program, write a message to the coach, ask questions, and enter measured blood pressure data). • Under supervision, patients perform one to eight exercises of their individualized exercise program.
Practice session 3 (optional)	• Under supervision, depending on the patients’ needs, they practice to interact with and navigate through the application menus (open exercise program, write a message to the coach, ask questions, and enter measured blood pressure data). • Under supervision, patients perform one to eight exercises of their individualized exercise program.

Practice sessions one to three will take place in the therapy facilities or the patient's room in the rehabilitation center. Between training sessions with personal contact, patients practice on independently, wear an activity tracker and measure blood pressure daily. Further, they receive coaching messages as well as questionnaires to complete, and they can contact their personal coach during regular working hours.

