### Measurement sessions, outcomes and outcome measures

2.4

Patients will be evaluated during three measurement sessions: before the begin of the START program (T1), at discharge (T4), and after completion of the 12-week program (T6). The 12-week program was implemented for two reasons. Firstly, the greatest functional improvements following a stroke are typically observed during the early subacute phase, particularly within the first three months. Secondly, this period coincides with the transition from inpatient to outpatient care and rehabilitation, which we aimed to support and evaluate. All visits will take place in the rehabilitation center. If it is the patient's wish, the last measurement session can take place at the patients' home. Table 3 provides an overview on all measurement sessions, outcomes and outcome measures.

**Table 3 T3:** Summary of scheduled visits, relevant procedures and duration for patients.

Investigation period	Place of visit	Event	Time point	Content	Duration
Enrolment	Inpatient rehabilitation	Patient information	Day −10 to 0	Study information	10 min
		T0	Day 0	Sign informed consent	5 min
		T1	Day 1–7	Baseline assessment: MoCA, mRS, EQ-5D-5l, SPPB, TUG, TIS	20–30 min
Interventional Phase		T2	Week 1 +/− 7 days	Practice session 1 • Introduction to the application Blended Clinic and the START program • Practice to interact with and navigate through the application menus under supervision • Perform 1 to 8 exercises of training program under supervision • Introduction to self-measurement and entering blood pressure values • Set up activity tracker	30–60 min
		Practice	4–14 days	• Patients practice exercises on their own • Patients wear activity tracker and measure blood pressure • Patients receive about 1 to 5 coaching messages • Patients fill in SIS, SF- 36, mRS	5–10 min per training
		T3	Week 2 +/− 7 days	Practice session 2 • Practice to interact with and navigate through the application menus under supervision • Perform 1 to 8 exercises of training program under supervision	30–60 min
		Optional T3b	Week 3 +/− 7 days	Practice session 3 (optional) • Practice to interact with and navigate through the application menus under supervision • Perform 1 to 8 exercises of training program under supervision	30–60 min
		T4	Discharge from inpatient centre	Patients fill in SIS, SF-36, mRS, LSA-G	30 min

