
#### The secondary outcomes comprise the following

2.4.2

•The Functional Independence Measure (FIM) to evaluate the functional status of patients after a stroke throughout the rehabilitation process. It consists of 18 items focusing on motor and cognitive function. Each category is rated on a 7-point rating scale (from 1 = <25% independence to 7 = 100% independence) (20, 21). The FIM score will be used as a descriptive parameter and is used as a standard evaluation at entry to and discharge from the inpatient period.•The Functional Ambulation Categories (FAC) rates ambulation ability, determining how much support a patient requires for walking on a six-point rating scale from zero = unable to walk or assistance by walking through two or more assistants to 5 = able to walk independently everywhere (22).•The Montreal Cognitive Assessment (MoCA) is a screening tool to evaluate mild cognitive dysfunction in different cognitive domains from zero to 30 (no cognitive dysfunction) (23).•The National Institute of Health Stroke Scale (NIHSS) is a widely used tool by health care providers to quantify the impairment caused by a stroke. It consists 11 items, each item scored between zero and four (24). The higher the total score, the more severe the impairment caused by a stroke. NIHSS score will be will be used as a descriptive parameter.•The Modified Rankin Scale (mRS) is a valid and widely used functional measure for patients after a stroke (24, 25). The scale evaluates the degree of disability or dependence in activities of daily living using a rating scale from zero (no symptoms at all) to six (dead).•The Stroke Impact Scale (SIS) is a self-reported questionnaire that evaluates disability and health-related quality of life after a stroke and is designed for repeated administration to track changes over time (26, 27). The SIS consists of eight subscales (strength, hand function, mobility, activity of daily living, emotion, memory, communication and participation) comprising a total of 59 questions. Patients can rate each item on a five-point rating scale (from 1 = could not do at all to 5 = not difficult at all). Final scores range from zero to 100. The SIS includes an extra question on how much the patient feels that she/he has recovered from stroke that is rated on a scale from zero to 100.•The 36-Item Short Form Healthy Survey (SF-36) is a generic patient-reported outcome measure that quantifies health status and measures health-related quality of life (28, 29). It consists of eight subscales (physical functioning, role limitations due to physical problems, general health perceptions, vitality, social functioning, role limitation due to emotional problems, general mental health, and health transition) with eight scales scores, which are the weighted sums of the questions in their subscale (zero to 100). The lower the score the higher the impairment.•The EuroQoL EQ-5D-5l is a patient-reported outcome measure regarding the patients' health-related quality of life (30). It consists of six questions about an individuals' quality of life in general, a visual analogue scale with a score from zero to 100 and descriptive questions about five dimensions: mobility, self-care, activity of daily living, pain and complaints, fear and depression. Each dimension can be evaluated using a five-point rating scale (from 1 = no problems/pain/fear at all to 5 = extreme problems/pain/fear). The descriptive system of the EQ-5D-5l produces a 5-digit health state profile, whereas the value sets are anchored on 11,111 representing complete health.•The German Life-Space Assessment (LSA-G) evaluates the patients' life space and range of mobility. The LSA-G consists of a questionnaire on five different life spaces: rooms besides the bedroom, area outside the house, neighborhood, town or city lived in, outside of the town or city lived in. For each life space individuals are asked whether they visited these spaces and how often, whether they needed assistive devices or personal assistance (31).•The patient's activity level will be assessed using the GENEActiv (Activinsights, Kimbolton, UK) activity tracker. The activity tracker is a lightweight and waterproof raw data accelerometer, designed for health care research and clinical trials. It allows to monitor physical activity, sleep and everyday living through measuring acceleration, posture changes, sleep/wake time, movement activity and intensity. Patients will wear the GENEActiv sensor during inpatient rehabilitation and during the last three weeks of the intervention period. Patients' time spent in different activity levels, steps per day, and energy expenditure will be determined.•An additional measure to evaluate the patients' physical performance is the Short Physical Performance Battery (SPPB) that combines the results of gait speed, chair raise and balance tests (32). The SPPB can be used as a predictive tool for possible impairments and can aid in the monitoring of function in older people. The scores range from zero = worst performance to twelve = best performance.•Blood pressure and heart rate will be measured with a digital blood pressure measurement device (Medisana BU 510, medisana GmbH, Neuss, Germany) provided by the study center. Patients are reminded to measure their blood pressure every morning using the digital blood pressure measurement device and enter their data in the mobile application. During their practice sessions with the therapist (one to three), patients practice the self-measurement. For further practice, patients will be provided a video with the instructions and they can contact their coach if they have questions.•The widely used and well accepted Timed Up and Go (TUG) test will be used to evaluate the patients' mobility and their risk of falling. Patients are asked to stand up from a chair, walk three meters, turn around, walk back and sit down. The time patients need to complete the task will be measured in seconds (33).•The Trunk Impairment Scale (TIS) assesses static (with three items) and dynamic (with four items, each repeated two or three times) sitting balance and trunk coordination (two items, each repeated twice) in sitting position in patients after a stroke (34). Score ranges from zero to 23, where the higher score indicates better balance and coordination.•Furthermore, a weekly reporting scheme will document progress of the investigation, serious and non-serious adverse events and device deficits. Potential harm will be assessed by the following measures: recurrent stroke, serious adverse events (death, life threatening, in-patient hospitalization or prolongation of existing hospitalization, persistent disability).

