•Sample size: ≥75% of targeted sample size will be achieved•Recruiting rate: ≥40% of informed patients will be enrolled•Drop-out rate: ≥80% of enrolled patients will complete study participation•Adherence: ≥70% of planned trainings will be completed•Stability and maintenance: ≤3 system failures per week•Safety: number of (serious) adverse events in <10% of all participants•SUS: scores above 70 represent an acceptable usability, with scores smaller than 50 being judged as unacceptable (16)•G-MAUQ: average scoring ≥4•AQUA: average scoring in each dimension ≥3•NPS: average satisfaction ≥50%•Satisfaction (VAS): average satisfaction ≥50%•Perceived change (VAS): health status at least remained the sameSecondary analysis will include descriptive statistics of all secondary outcome variables and pre-post comparisons of clinical and performance-based parameters. Raw count (absolute and relative frequencies (*n*, %) will be presented for count and nominal data, medians (range, 25th and 75th percentiles) will be reported for ordinal data and mean (including standard deviation) will be reported for continuous data. Regarding pre-post comparisons, Wilcoxon signed-rank test will be used for ordinal data and *t*-test for continuous data after testing for normal distribution graphically using QQ-Plot and analyzed using the Shapiro-Wilk test. Significance will be determined with *p*-value of ≤0.05.

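### Unadjusted pre-post tests at p≤0.05 in a single-arm study cannot inform on START, and a paired t-test on Timed Up and Go seconds loses patients who cannot do the test

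*Protocol article*

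**What the plan says.** Section 2.1 describes a "single-centered observational descriptive feasibility trial", with no comparison group. For the secondary analysis, section 2.5 announces "pre-post comparisons of clinical and performance-based parameters". The rule is "Regarding pre-post comparisons, Wilcoxon signed-rank test will be used for ordinal data", and a t-test for continuous data after a normality check. It closes with "Significance will be determined with *p*-value of ≤0.05". No adjustment for the number of tests is stated, the outcomes to be tested are not listed, and the visits that form pre and post are not named.

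On what else changes during the study, section 2.4 justifies the 12-week programme partly because "the greatest functional improvements following a stroke are typically observed during the early subacute phase, particularly within the first three months". Section 2.3.1 introduces the inpatient START sessions with "Besides their multi-disciplinary therapy schedule".

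On TUG, section 2.4.2 says "The time patients need to complete the task will be measured in seconds" and gives no value for a patient who cannot perform it. Table 1 admits "Modified Rankin Scale score 1–5" and requires no walking ability. The lowest Functional Ambulation Category (FAC) in section 2.4.2 covers patients unable to walk. Table 3 schedules TUG at T1 and T6 only.

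**The concern.** A paired test of no change answers whether patients differ between two visits. In one group, that difference mixes any effect of START with the improvement expected after stroke, usual therapy and everything else that happens between the visits. The null hypothesis may well be false whether or not START does anything, so rejecting it says nothing about START. An adjustment for multiple tests would not cure this, because attribution is the first problem and multiplicity the second.

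What is at stake is how the results are read. The discussion gives this study a central role in planning a later randomised trial. A list of significant improvements could be taken there as a sign of efficacy, or as a basis for its assumptions.

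The TUG problem is separate. A time in seconds does not exist for a patient who cannot do the test, so that patient has no paired difference. The mean change then describes only patients able at both visits. It omits those who gained or lost the ability, which may be the largest functional changes in the sample.

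**Working it through.** **The plan's own figure.** The sample size of 40 is a convenience number within a cited range of 24 to 50, which it satisfies. No alpha, power or effect size lies behind it, so there is no calculation to reproduce.

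**Number of pairs.** The completion criterion is 80%: 0.80 × 40 = 32 pairs. If only 75% of the target is enrolled, 0.75 × 40 = 30 and 0.80 × 30 = 24 pairs.

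**Background change unrelated to START.** Let d be the mean paired change divided by its standard deviation. The chance of p≤0.05 in a two-sided paired t-test is P(|T| > t(0.975, n−1)), with T noncentral t on n−1 degrees of freedom and noncentrality d√n. Two-sided testing is assumed, since the text does not state it. The documents give no d, so a range is shown:

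| d | n = 24 | n = 32 | n = 40 |
|---|---|---|---|
| 0.2 | 0.156 | 0.195 | 0.235 |
| 0.3 | 0.291 | 0.376 | 0.457 |
| 0.5 | 0.650 | 0.782 | 0.869 |
| 0.8 | 0.963 | 0.992 | 0.999 |

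At n = 32 an observed d of about 0.36 is enough for p≤0.05. Simulated Wilcoxon tests at n = 32 give nearly the same: about 0.37, 0.76 and 0.98 at d = 0.3, 0.5 and 0.8.

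**How many tests.** Section 2.5 gives no list, so the count is a range built from section 2.4.2 and Table 3.
- Scores scheduled at both T1 and T6: modified Rankin Scale (mRS) 1, EQ-5D 2, Short Physical Performance Battery (SPPB) 1, TUG 1, Trunk Impairment Scale (TIS) 1. Total 6.
- Adding blood pressure 2, heart rate 1 and activity 3: total 12.
- Adding the Stroke Impact Scale (SIS) 9, SF-36 8, Life-Space Assessment (LSA-G) 1 and Functional Independence Measure (FIM) 1: total 31. FIM is labelled descriptive and may not be tested. FAC is left out because Table 3 schedules it only at T6.

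**Multiplicity if nothing changed.** For k independent tests the chance of at least one p≤0.05 is 1 − 0.95^k:
- k = 6: 1 − 0.95^6 = 0.265
- k = 12: 1 − 0.95^12 = 0.460
- k = 30: 1 − 0.95^30 = 0.785, with 30 × 0.05 = 1.5 expected

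Subscales of one questionnaire are not independent. With 30 tests simulated at a common correlation of 0.3, 0.5 or 0.7, the chance falls to about 67%, 51% or 34%. Half of such chance findings would point to worsening.

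These figures and those in the table describe different situations, the first with no change at all and the second with real background change, and should not be added together.

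**TUG.** The share of patients unable to perform it is not given. If 10% to 40% cannot do it at one visit or the other (an assumption), 32 pairs shrink to between 29 (32 × 0.9) and 19 (32 × 0.6), and 40 pairs to between 36 and 24. The loss is not at random, since it depends on the outcome itself.

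**The case against.** The strongest defence is that nothing in this study turns on these tests. The hypothesis concerns feasibility, the secondary aim is descriptive, the 12 feasibility criteria contain no pre-post test, and efficacy is left to a later randomised trial. This stands. A reader might infer that significant p-values feed the judgement that START is feasible and useful, but the criteria in section 2.5 do not support that.

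A reader might also infer that some 30 significant improvements are bound to appear through natural recovery. The documents do not support this either. They speak of functional improvements without calling them natural and give no size. At d = 0.2 only about one outcome in five would be significant. Eligibility sets no limit on time since stroke, so some follow-up may fall outside the period of greatest improvement. The figure of 30 tests requires that all patient-reported subscales are tested, and 79% further requires independence.

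On TUG, the article states no rule that drops patients who cannot walk, and a rule for inability may exist in the full protocol or analysis plan. SPPB and FAC do score such patients, so mobility does not rest on TUG alone. But the article does fix a measure in seconds and a t-test for continuous data, and together these leave no difference to analyse when either visit has no time. Nor can the direction of any bias be stated: patients who gain the ability, lose it, or lack it throughout are all lost.

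Finally, section 2.5 says data from all participants will be analysed, so a restriction to study completers is not stated. A paired test needs only the two visits chosen, which the article does not name.

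**Conclusion.** The point holds as one of interpretation. Section 2.5 fixes an unadjusted significance criterion for change in one group, in a setting where the protocol itself expects change. The resulting p-values cannot inform on START. With 32 pairs the share of outcomes reaching p≤0.05 runs from about 20% to 99% as the assumed background change goes from d = 0.2 to 0.8. With no change at all, at least one chance finding has a probability of about 26% to 46% for 6 to 12 independent tests and at most about 79% for 30. These figures rest on assumed effect sizes, two-sided tests and 80% completion. The feasibility decision is unaffected.

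The TUG point holds as a consequence of two rules in the article, seconds only and a paired t-test, given eligibility up to mRS 5 and a foreseen FAC of 0. How many patients it would affect is unknown. It is worth correcting because the change is nearly free.

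**What to change.** In section 2.5, remove the p≤0.05 criterion, or label the tests exploratory. Report mean or median change with 95% confidence intervals, described as change over time that is not attributable to START. List the outcomes and name the two visits compared for each.

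For TUG, report the proportion able to perform it at T1 and at T6. Analyse the change by signed ranks with inability as the worst rank, so that gaining the ability counts as an improvement and losing it as a worsening. Mean seconds among patients able at both visits can be kept as a supplement, labelled as that subset.

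For outcomes with three or more scheduled visits (mRS, SIS, SF-36, LSA-G), a repeated-measures analysis using all available visits is an optional gain. It offers nothing for EQ-5D, SPPB, TUG and TIS, which Table 3 schedules only at T1 and T6.

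The cost is a change of analysis wording, with no new data. There would be no p-values to quote as evidence of change, and TUG change would no longer be summarised by mean seconds alone.
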